## Abstract

**Background:**

Children with disabilities attending special education schools face significantly higher risks of oral diseases, particularly dental caries, due to physiological, cognitive, and environmental challenges. However, school-based oral health interventions targeting this population are limited in China.

**Objective:**

This study aims to assess the effectiveness of fluoride varnish (FV) application, delivered alongside oral health education for parents and teachers, in improving the oral health of students in special education schools in Guangdong Province.

**Methods:**

This is a stratified, cluster randomized controlled trial conducted in Guangdong Province, China. Schools will be stratified by regional economic development level and randomly assigned to either an intervention or control group. The intervention group will receive annual dental examinations, biannual FV applications, and oral health education. The control group will receive standard annual examinations and comparable oral health education. Participants will be students aged 5 to 22 years enrolled in selected special education schools. Baseline assessments and 12-month follow-ups will include oral examinations and questionnaires assessing oral health knowledge, attitudes, and behaviors. The primary outcome is the difference in caries prevalence between the intervention and control groups at follow-up. Secondary outcomes include changes in oral hygiene behaviors and caregiver knowledge. Data will be analyzed using multivariable regression models adjusting for potential confounders and clustering effects.

**Results:**

This trial was funded by the Department of Education of Guangdong Province in 2025 (grant YCKJ-2025-30). As of June 2025, 12 special education schools across 3 cities had been enrolled (n=7, 58.3% intervention and n=5, 41.7% control schools), and more than 1100 students had been recruited. Baseline data collection and the first FV application are complete. Follow-up data collection is ongoing and is expected to conclude in June 2026. Data analysis has not yet started, and results are expected to be published in 2027.

**Conclusions:**

Biannual application of FV is expected to significantly reduce caries prevalence and improve oral hygiene behaviors among students in special education schools. This school-based intervention model aims to provide a scalable and evidence-based strategy to mitigate oral health inequities for children with disabilities in China.

## Introduction

Oral health is a critical component of general health and quality of life, yet children with disabilities remain an underserved population with significantly elevated risk for oral diseases [1,2]. Studies across multiple settings have consistently shown that students with disabilities experience a higher prevalence and severity of dental caries, gingival inflammation, and oral hygiene problems than their peers without disabilities [3]. This disparity is attributed to a range of factors, including motor or cognitive impairments, reduced self-care abilities, dependence on caregivers, behavioral challenges, and limited access to dental services [3,4]. In China, these challenges are compounded by underdeveloped oral health support systems within special education settings, despite national goals to promote equitable health access for all populations [5].

Fluoride varnish (FV) is widely endorsed as an effective caries-preventive intervention, particularly in children at moderate to high risk [6,7]. Meta-analyses, including multiple Cochrane reviews encompassing more than 200 trials and 80,000 participants, have consistently reported significant reductions in caries incidence, up to 43% in permanent teeth and 37% in primary teeth, with biannual professional FV application [6-9]. Additional studies have demonstrated its efficacy in preventing white spot lesions in adolescents with orthodontic appliances and reducing caries in special-needs populations, such as children with attention-deficit/hyperactivity disorder [10,11]. However, the overall body of evidence remains inconclusive. Some more recent systematic reviews and large-scale trials have shown limited or no significant benefit, particularly in low-risk populations or settings with high background fluoride exposure [7,12]. Furthermore, substantial heterogeneity across studies, limited methodological quality in earlier trials, and uncertainty in comparative effectiveness vs other preventive interventions (eg, sealants) complicate interpretation [9,13]. This conflicting evidence underscores the need for rigorously designed, context-specific evaluations of FV effectiveness, particularly in high-risk, underserved populations, such as children with disabilities in school-based settings.

To date, few randomized trials have evaluated FV as a standalone intervention in students attending special education schools, especially in low- and middle-income countries [3,11]. Existing research often combines FV with other interventions, targets only certain subtypes of disabilities (eg, intellectual disability), or lacks sufficient sample sizes and follow-up to assess effectiveness under real-world conditions [11]. In China, there is currently no trial evaluating the effect of FV in special education settings, nor any that incorporate systematic delivery through existing school health infrastructure.

This study addresses this critical evidence gap by evaluating a school-based FV intervention in special education schools in Guangdong Province, China, using a stratified cluster randomized controlled trial (RCT) design. The trial compares the effect of biannual FV applications, administered by trained professionals and accompanied by tailored oral health education for parents and teachers, with that of standard care alone. By assessing the impact of FV in a high-risk, underserved population, this study seeks to generate policy-relevant evidence to inform national oral health strategies for children with disabilities.

## Methods

### Study Design

This study is a stratified cluster RCT designed to evaluate the effectiveness of FV in preventing dental caries among students attending special education schools in Guangdong Province, China. This trial is open label. Neither participants, caregivers, nor outcome assessors will be blinded to group allocation due to the nature of the intervention.

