### Study Outcomes

The primary outcome of this study is the prevalence of dental caries among students at 12 months following the intervention. Dental caries will be assessed through clinical oral examinations using the decayed, missing, and filled teeth index (DMFT) for permanent and primary dentition, respectively. These examinations will be conducted in accordance with the national standardized child oral health survey protocol used in China. Briefly, trained and calibrated dental professionals will perform tooth-level examinations using disposable dental mirrors and probes under natural or portable lighting. Dental status for both primary and permanent teeth, including caries experience and related conditions, will be recorded. Examinations will take place in a designated room with adequate lighting [21]. Children will be assessed while seated [22], and wheelchair users will remain in their own wheelchairs. Two familiar teachers or school support staff will attend to assist with communication and comfort [23]. A trained dentist will conduct the examination, and a trained nurse will record the number of decayed, missing due to caries, and filled teeth per child. The blank recording form is provided in Figure 3. To minimize measurement bias, examiners conducting the follow-up assessments will be blinded to the school allocation status.

Secondary outcomes include (1) oral hygiene status (eg, presence of plaque and gingivitis), assessed using gingival health indicators and plaque indices; (2) changes in oral health–related knowledge, attitudes, and practices (KAP) among students, parents, and teachers, measured using a structured questionnaire adapted from the Third National Oral Health Survey [24].

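### The protocol says both that outcome assessors will know the allocation and that the follow-up examiners who score the primary outcome will not

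*Protocol article*

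**What the plan says.** Study Design declares "This trial is open label" and then "Neither participants, caregivers, nor outcome assessors will be blinded to group allocation due to the nature of the intervention". No visit, outcome or type of assessor is excepted.

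Study Outcomes defines the endpoint: "The primary outcome of this study is the prevalence of dental caries among students at 12 months following the intervention". It is measured by clinical examination, in which "trained and calibrated dental professionals will perform tooth-level examinations using disposable dental mirrors and probes under natural or portable lighting". A dentist examines and a nurse records. The same section ends its account of the examination with: "To minimize measurement bias, examiners conducting the follow-up assessments will be blinded to the school allocation status".

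Two other facts from the article bear on this. Under Intervention and Control, varnish is applied at month 0 and month 6, also by trained dental professionals. Under Study Outcomes, "Two familiar teachers or school support staff will attend to assist with communication and comfort" at each examination.

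**The concern.** One section denies, for the people who score the primary outcome, the safeguard that another section promises. A site team cannot follow both, and a reader of the results could not tell which was followed.

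Whether a tooth counts as decayed under mirror and probe, and how plaque and gingival condition are graded, depends on the examiner's judgement. If the examiner knows the school's arm, scores can drift with expectation. Schools are the unit of allocation and there are only 12 of them, so learning one school's arm reveals the arm of every child examined there. A bias of this kind does not shrink as more students are enrolled, and it cannot be taken out after the data are collected.

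**Working it through.** The check is mainly a comparison of text. No arithmetic decides it.

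1. **Do the two statements concern the same people?** The primary outcome is caries at 12 months, scored at the follow-up oral examination (Study Outcomes). Those who conduct that examination are therefore the outcome assessors for the primary outcome. They also record the plaque and gingival indices (Data Collection).

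2. **Do the statements conflict?**
   - Study Design: outcome assessors know the allocation; no exception is given.
   - Study Outcomes: follow-up examiners do not know the allocation; the purpose given is to limit measurement bias.
   - For the 12-month examiners these are opposites.

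3. **Does another section reconcile them?** Stratification, Randomization, and Allocation Concealment describes sealed envelopes and disclosure after school enrollment. That protects the assignment of schools, not the later scoring. Data Collection, Statistical Analysis and Results are silent on blinding. Strengths and Limitations names generalizability as its only limitation and does not mention unblinded scoring.

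4. **Does the stated reason support no blinding of examiners?** The last varnish application is at month 6 and the examination is at month 12, so the gap is 12 − 6 = about 6 months. A visible procedure explains why children and caregivers cannot be blinded. It does not by itself stop an examiner from being kept unaware half a year later, and Study Outcomes shows that the sponsor regards this as feasible.

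5. **Would the analysis repair it?** The mixed-effects models and robust standard errors in Statistical Analysis deal with correlation within schools. They do not correct scores that differ systematically by arm. If knowledge of allocation changed the caries status of a net share *s* of intervention students in one direction, the estimated prevalence difference would move by *s*, whatever the sample size. The article gives nothing from which *s* could be estimated.

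6. **Does a planned figure change?** The sample size reproduces from its own inputs:
   - (1.96 + 1.28)² × (0.24 + 0.24) / 0.20² = 125.97, rounded to 126 per group;
   - design effect 1 + 149 × 0.02 = 3.98, and 126 × 3.98 = 501.5, stated as 501;
   - 501 / 0.9 = 556.7, rounded to 557.

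   Blinding enters none of these steps, so the figure is the same whichever statement is kept.

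**The case against.** The best defence is that Study Outcomes is the specific statement: it sits in the outcome section, names the follow-up examiners and gives a purpose. Study Design would then be a loose open-label sentence, perhaps with the parent and teacher questionnaires in mind. Part of this stands. The safeguard is written down, so it would be wrong to say that the plan offers none. The narrow reading of Study Design does not stand, because the sentence is unqualified and speaks of assessors in general.

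It can also be said that examiners are calibrated and follow a national survey protocol. That reduces variation between examiners, but it does not replace blinding.

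Three stronger readings are tempting, and the document does not support them:

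- **The staff who varnish a school will also score it.** Both groups are described as trained dental professionals, but a shared job title does not show shared personnel. An article may leave team rosters to the full protocol.
- **The bias would be as large as the effect sought.** The only planned difference in the article is 60% against 40%, that is 20 points. Net misscoring of 3% to 5% of intervention students, a pure assumption, would shift prevalence by 3 to 5 points, or 3/20 = 15% to 5/20 = 25% of that difference. Because missing and filled teeth also count, rescoring one tooth often leaves a student's status unchanged.
- **The result will be biased towards varnish.** This is a risk with a plausible direction, not a certainty.

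**Conclusion.** The contradiction is real. It concerns the examiners who score the primary outcome and the clinical secondary outcomes, and nothing else in the article resolves it. It needs correcting before the 12-month examinations. On the article's timeline, follow-up is still under way and ends in June 2026, so there is time to do so.

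What is at stake is risk of bias and the credibility of the reported result, not sample size or significance level. The size of any bias cannot be derived from the document. The conclusion rests on two premises: that caries, plaque and gingival scoring involves examiner judgement, and that the month-12 examiners are the outcome assessors. It does not depend on any assumption about who staffs the varnish and examination teams.

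**What to change.** 1. In Study Design, remove outcome assessors from the list of those who are not blinded. Participants and caregivers stay on it.
2. Make the Study Outcomes statement the governing rule for the 12-month examinations and add how it is kept:
   - examiners and recorders are not given the allocation;
   - as far as the existing teams allow, nobody scores a school where they applied varnish;
   - school staff who attend are asked not to disclose the school's arm.
3. If blinding cannot be achieved in practice, correct Study Outcomes instead and add unblinded outcome assessment to Strengths and Limitations.

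Recording each examiner's guess of a school's allocation would help in judging whether blinding held, but it is optional.

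The cost is a change of wording and a small scheduling effort across the 12 schools. The article does not give the number of examiners or teams, so it cannot be said in advance whether full separation is possible without extra staff. That is why the second safeguard is limited to what the teams allow.

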### Setting

All special education schools located in Guangdong Province are eligible for inclusion if they provide primary and/or secondary education to students with disabilities. No minimum enrollment threshold is required, and schools are not excluded based on size or student composition. All participating institutions are formally registered educational entities operating under the supervision of local education authorities. According to the Guangdong Provincial Education Bureau, there are a total of 162 special education schools distributed across 21 prefecture-level cities. Cities such as Guangzhou (n=19, 11.7%), Shenzhen (n=11, 6.8%), and Shantou (n=8, 4.9%) have relatively higher concentrations of eligible schools. The sampling frame for this trial was constructed using the official registry of special education schools.

### Stratification, Randomization, and Allocation Concealment

Guangzhou, representing a high economic development region within the Pearl River Delta along with Yunfu and Heyuan, which represent middle-to-low development regions from western and northern Guangdong, respectively, were purposively selected to ensure geographic and socioeconomic diversity. Within each of these 3 cities, eligible schools were identified from lists of schools willing to participate provided by local education authorities. School-level cluster randomization was then performed stratified by city. A computer-generated random allocation sequence was produced by an independent statistician who was not involved in school recruitment, baseline assessment, or intervention implementation. Schools within each city were randomly assigned to either the intervention or control group according to this sequence. To ensure allocation concealment, opaque, sealed envelopes containing group assignments were prepared by staff not involved in intervention implementation. Allocations will be disclosed only after completion of school enrollment. Ultimately, 5 control schools and 7 intervention schools were selected across the 3 cities to participate in the study (Figure 1).

**Figure 1. F1:**
[figure not shown]
Flow diagram of school selection for the cluster randomized controlled trial.

### Inclusion and Exclusion Criteria

Students enrolled in participating schools will be recruited, with informed consent obtained from their legal guardians.

Students will be excluded if they have bronchial asthma, a known severe allergy or hypersensitivity to FV. They will also be excluded if they have acute oral conditions or severe systemic diseases. Students who are unable to cooperate or refuse to participate in the study will also be excluded.

### Sample Size

The primary outcome of this study is the prevalence of dental caries at 12 months. On the basis of previous literature in comparable populations, the prevalence of caries among students in special education schools without intervention is estimated at 60% [5,14]. A reduction to 40% in the intervention group is considered clinically and politically meaningful [9,15]. Using a 2-sided α of .05 and a power of 90% (β=.10), the required sample size per group for an individually randomized trial is estimated using the formula:

$$n=\frac{{\left(z_{\alpha /2}+Z_{\beta }\right)}^{2}\times \left(p_{1}(1-p_{1})+p_{2}(1-p_{2})\right)}{{\left(p_{1}-p_{2}\right)}^{2}}$$

where *z*_*α*/2_ is 1.96, *Z*_*β*_ is 1.28, *p*_1_ is 0.60, and *p*_2_ is 0.40. Substituting these values gives a sample size of approximately 126 per group under individual randomization. Additionally, this study uses a stratified cluster RCT design, which requires adjustment for clustering using the design effect. The design effect was calculated as 1+(m–1)×*ρ* where *m*=150 (average cluster size, ie, school size), *ρ* is 0.02 (intracluster correlation coefficient). The resulting design effect was calculated as 3.98, yielding an adjusted sample size of 501 students per group. Allowing for an anticipated 10% dropout rate, the final required sample size is 557 students per group, totaling 1114 participants across all clusters. On the basis of the final required sample size of 557 students per group and an average cluster size of 150 students per school, the required number of clusters was calculated as 557/150=3.71 per group. Therefore, at least 4 schools per group, corresponding to a minimum of 8 clusters in total, are required.

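### The stated 8-school minimum gives about 83% power (74% with city strata fitted), not 90%, and the calculation was not restated for the 12 schools enrolled

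*Protocol article*

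**What the plan says.** The Sample Size section takes a two-sided 5% level, 90% power, control prevalence 60%, intervention prevalence 40% and an ICC of 0.02. It finds 126 students per group under individual randomisation, a design effect of 3.98 and 501 per group. After 10% dropout, "the final required sample size is 557 students per group, totaling 1114 participants across all clusters". It then divides 557 by "an average cluster size of 150 students per school", obtains 3.71 and rounds up: "Therefore, at least 4 schools per group, corresponding to a minimum of 8 clusters in total, are required".

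The abstract's Results paragraph reports that "12 special education schools across 3 cities had been enrolled", 7 intervention and 5 control, and that "more than 1100 students had been recruited". The section on stratification and randomisation and the main Results section give the same 7:5 split. Randomisation was stratified by city. The Setting section sets no minimum enrolment and excludes no school on size. The Statistical Analysis section accounts for clustering by robust standard errors or multilevel modelling.

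**The concern.** Two things do not fit.

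- **The last step of the calculation.** Dividing students by school size treats a school as a container for students. The school is the randomised unit, so the number of schools also fixes the degrees of freedom for the treatment comparison. With 8 schools the critical value is well above 1.96, and a calculation based on 1.96 and 1.28 overstates power.
- **The inputs.** 150 students per school and two equal groups are not the design that was enrolled.

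At stake is whether a reader can rely on the stated 90%, and whether another team could safely copy the 8-school minimum for a similar trial.

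**Working it through.** **Reproducing the plan's figure** (all inputs from Sample Size)

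- n = (1.96 + 1.28)² × (0.24 + 0.24) / 0.20² = 125.97, so 126.
- Design effect = 1 + (150 − 1) × 0.02 = 3.98.
- 125.97 × 3.98 = 501.4, so 501; 501 / 0.9 = 556.7, so 557.
- 557 / 150 = 3.71, rounded up to 4 per group.

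Every step reproduces under the plan's formula.

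**Power at 4 + 4 schools**

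Students analysed per school: 150 × 0.9 = 135. Design effect: 1 + 134 × 0.02 = 3.68.

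Standard error of the difference: √[0.24 × 3.68 × 2 / (4 × 135)] = 0.0572. Standardised effect: 0.20 / 0.0572 = 3.50.

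| Reference | Critical value | Power |
|---|---|---|
| Normal | 1.96 | 93.8% |
| t, 8 − 2 = 6 df | 2.447 | 82.8% |
| t, 4 df (2 more spent on three cities) | 2.776 | 74.4% |

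The t rows use the non-central t distribution. A beta-binomial simulation of school-level proportions (200,000 runs) gives 82.2% and 73.9%. In the same simulation, the 1.96 cut-off has a true type I error of about 10%, or 12% with strata fitted, so the 93.8% is not power at a 5% level.

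With 5 schools per arm of 135, power is 92.7% on 8 df and 90.0% on 6 df.

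**The enrolled design**

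- Average school size: 1100 / 12 = 91.7, against 150 planned (12 × 150 would be 1800).
- After 10% loss: 82.5 per school. Design effect at ICC 0.02: 1 + 81.5 × 0.02 = 2.63.
- Standard error: √[0.24 × 2.63 × (1/(5 × 82.5) + 1/(7 × 82.5))] = 0.0512. Standardised effect: 3.905.

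For unequal school sizes the design effect becomes 1 + [(1 + CV²) × m − 1] × ICC. Power for 60% versus 40%:

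| ICC | School-size CV | t(10) | t(8), city fitted |
|---|---|---|---|
| 0.02 (plan) | 0 | 93.9% | 92.6% |
| 0.02 (plan) | 0.6 (assumed) | 88.7% | 86.9% |
| 0.05 (assumed) | 0 | 71.7% | 69.3% |
| 0.10 (assumed) | 0 | 47.3% | 45.3% |

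**What the plan's formula needs at the enrolled school size**

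Design effect: 1 + (91.7 − 1) × 0.02 = 2.81. Then 125.97 × 2.81 = 354 per arm, and 354 / 0.9 = 394 after dropout.

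**The case against.** The plan calls 8 schools a minimum, and 12 were enrolled. At the plan's own ICC and effect, with equal school sizes, those 12 have 92.6% to 93.9% power even on a t reference. No step of the arithmetic is wrong. This all stands: the fault is one of method and of a justification left unrevised, and it does not show a shortfall in the trial being run.

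The 74% figure is also the less secure end. City is not among the covariates named in the Statistical Analysis section, and the figure charges stratification for degrees of freedom without crediting any between-school variance that stratification or baseline adjustment might remove. On the document's inputs alone, 83% is the figure to quote. It is still below 90%.

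A reader might infer that the control arm misses its target, because five schools of 91.7 hold about 458 students rather than 557. The documents do not support that. Students per arm are not reported, so 458 assumes equal schools. More importantly, 557 belongs to schools of 150; at about 92 per school the same formula needs about 394 per arm, which 458 exceeds. The total of more than 1100 is also compatible with 1114.

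A reader might likewise take the figures at ICC 0.05 or 0.10 as the trial's real power. Those ICCs and the CV of 0.6 are assumptions of this review, and nothing in the documents shows that 0.02 is wrong. They belong in a sensitivity range.

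**Conclusion.** The point holds as a correction to the stated justification. The claim that 8 schools give 90% power is wrong by about 7 percentage points on 6 df, and by about 16 if city is fitted. The planning inputs of 150 per school and equal groups do not describe the 7-versus-5 trial with about 92 students per school.

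No loss of power below 90% is shown for the enrolled trial at ICC 0.02 with equal school sizes. Its margin is thin, though: an assumed size CV of 0.6 takes it just under 90%, and an assumed ICC of 0.05 takes it to about 70%. All these figures are for the plan's 60% versus 40% effect, assume 10% loss spread evenly over schools, and take no credit for baseline adjustment, as the plan's own calculation does not.

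**What to change.** In Sample Size:

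1. Withdraw the statement that 4 schools per group, 8 in total, suffice for 90% power.
2. Keep 557 per group and 1114 in total, labelled as the pre-enrolment planning calculation, so that the a priori basis stays on record.
3. Add the power of the enrolled design: 7 versus 5 schools, the actual school sizes and their CV, a t reference with between-school degrees of freedom, and ICC 0.02 alongside a range of higher values marked as assumptions (for example 0.05 and 0.10).

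Do not enrol more schools or students on this account. The cost is one recalculation from school sizes the team already holds and a few sentences of text. The stated power will look less favourable at ICCs above 0.02. Data analysis has not started, so the restatement can be made without knowledge of results.
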